#### Statistical analysis

Preliminary analyses will include descriptive statistics, analyses of variance and chi-square tests to examine group differences in baseline variables. If any differences are found, these variables will be entered as covariates in outcome analyses. Pattern mixture analyses will examine selection bias by comparing the characteristics and outcomes of participants who completed the study to those who did not both across and within study groups. Alpha will be set to .05, and adjusted for multiple comparisons if needed. Missing values are expected, and will be handled using methods such as multiple imputation, maximum likelihood estimation, and intent-to-treat analyses. The primary outcome is biochemically verified 7-day ppa (1 = cessation, 0 = smoking) at 6-months. Generalized linear mixed models (GLMMs) will test the longitudinal effect of intervention condition on abstinence, including interaction terms and adjusting for covariates. Controlling for covariates, hierarchical logistic regressions will determine the odds of abstinence at the 3-month follow-up (secondary outcome), and treatment engagement and potential moderating variables (e.g., acculturation, ethnic identify, readiness to quit) will be analyzed with analyses of covariance and hierarchical regression analyses.

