**Methods:**

This study is a 3-arm semi-pragmatic randomized controlled trial (RCT). Participants will be 1050 enrollees in the North Carolina State quitline (QuitlineNC) who self-identify as African American. Usual quitline care includes up to 4 proactive quit coaching calls, website access, and two-weeks of nicotine patch therapy. Eligible study participants will be randomized to receive (1) standard quitline services plus *PTF (PTF)*; (2) quitline services plus a standard tobacco cessation DVD (attention control); or (3) quitline services alone (usual care). Assessments will be conducted at baseline, 3 and 6-months post-enrollment. The primary outcome will be biochemically verified 7 day ppa at 6-months. Generalized linear mixed models (GLMMs) and hierarchical logistic regression will be used to assess the effects of treatment group on cessation outcomes and to test potential moderators.

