### Randomization

The individual is the unit of randomization. The randomization scheme was developed using a computer-generated random numbers table. We are using stratified random sampling (by sex) with equal allocation to conditions. Randomization occurs through an automated algorithm after Quit Coaches® indicate within the computer system that a participant has provided verbal consent. Participants are blind to their intervention condition.

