### Measures

#### Baseline (Table 1)

Standard quitline enrollment items include demographics, tobacco use history (age of initiation, current smoking, daily smoking, types of products used, history of quit attempts, prior use of quitline/telephone counseling services), time to first cigarette, health insurance, chronic medical conditions (e.g., asthma, cancer), stage of readiness to quit, and electronic cigarette use. Study-specific measures include readiness to quit [22], perceived stress [23], depressive symptoms [24], acculturation [25], ethnic identity [26], ethnic discrimination scale [27], culturally specific intervention expectancy, and social support [28]. Measures are minimized to reduce participant burden.

**Table 1 Tab1:** Study Specific Data Collection

Measure	Baseline	3-Month Follow-Up	6-Month Follow-Up
Demographics	X		
Tobacco Use	X		
Weight concerns	X		
Readiness to Quit	X	X	X
Perceived Stress	X	X	X
Depressive Symptoms	X	X	X
Acculturation	X		
Ethnic Identity	X		
Expectancies for Culturally Specific Interventions	X		
Perceived Social Support	X	X	X
Perceived Ethnic Discrimination	X		
Treatment Engagement		X	X
Treatment Utilization		X	X
TNP Use		X	X
Intervention Ratings		X	
Time-Line Follow-Back (smoking pattern)		X	X
Cotinine^a^			X

^a^Saliva for cotinine analysis is collected from self-reported abstainers only

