### Data analyses

#### Sample size and power

Previous research found 10–29% quit rates among African American quitline callers [9]. Our preliminary research showed a 7% difference in self-reported verified cessation, between participants who received only the *PTF* DVD vs. the Standard control (no additional counseling or NRT). Using the formula provided in Diggle et al. [33] (p. 31), we anticipated a 7% difference in 7-day ppa at 6-months between the *PTF* (32%) vs. control (25%) conditions, with a power of .80, alpha of .05, which requires 350 participants/condition.

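### Covariates for the outcome models are chosen by testing baseline differences between arms, a rule that follows chance imbalance and gives the stratification factor, sex, almost no route into the model

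*Protocol article*

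**What the plan says.** The Statistical analysis section of the protocol article opens with a testing step: "Preliminary analyses will include descriptive statistics, analyses of variance and chi-square tests to examine group differences in baseline variables". The next sentence turns the result into a modelling rule: "If any differences are found, these variables will be entered as covariates in outcome analyses".

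The covariates so chosen feed the outcome models. For abstinence the text says: "Generalized linear mixed models (GLMMs) will test the longitudinal effect of intervention condition on abstinence, including interaction terms and adjusting for covariates". The logistic regression for 3-month abstinence is also described as controlling for covariates. No covariate is named for any of these models, and the baseline-test rule is the only selection rule given.

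The Randomization section says: "We are using stratified random sampling (by sex) with equal allocation to conditions". Nowhere does the article say that sex will be in an outcome model.

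The significance level appears only in general terms: "Alpha will be set to .05, and adjusted for multiple comparisons if needed". Whether that level, or the adjustment, applies to the baseline tests is not said.

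**The concern.** Participants are randomised individually, so if the allocation is sound, any baseline difference between arms is chance. A significance test of that difference cannot show whether the variable needs adjustment. What makes a baseline variable worth adjusting for is that it predicts quitting, and the rule does not look at that. It brings in variables that happen to be imbalanced even if they are unrelated to abstinence, and passes over strong predictors that happen to be balanced.

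Three things are at stake.

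- **The model is not fixed in advance.** Its covariates depend on which baseline tests fall below the threshold.
- **The estimated quantity can shift.** In a logistic GLMM the treatment odds ratio is conditional on the covariates in the model, so adding or dropping a prognostic variable changes what is estimated as well as how precisely.
- **The stratification factor is passed over.** Stratification exists to balance sex, so a rule that admits only imbalanced variables works against including the one factor the design balances.

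**Working it through.** **The plan's own figure.** The article gives no number for this point. The power check below uses its design figures, "32%) vs. control (25%) conditions, with a power of .80, alpha of .05, which requires 350 participants/condition", so I recomputed those first. For a simple two-sided comparison of two proportions (p̄ = .285):

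n = [1.960 × √(2 × .285 × .715) + 0.842 × √(.32 × .68 + .25 × .75)]² / .07² = (1.251 + 0.536)² / .0049 ≈ 652 per arm.

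This does not reproduce 350. At 350 per arm the same formula gives power of 53.7%. A repeated-measures version reaches about 350 only with values the article does not give (for example, two measurements with a correlation near 0.07). That is a separate matter. Here 350 per arm with 25% vs 32% serves only as the setting in which analyses are compared.

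**Step 1: how often the rule selects something.** For k independent tests at .05, P(at least one) = 1 − .95^k.

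| Candidate variables | Source of k | Expected number | P(at least one) |
|---|---|---|---|
| 11 | baseline rows of Table 1 | 0.55 | 43% |
| 20 | items in the Baseline measures text (12 enrolment, 8 study-specific, demographics counted once) | 1.0 | 64% |
| 30 | assumed, demographics and tobacco items split further | 1.5 | 79% |

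Independence is an assumption. Several items are plainly related, which would lower these figures. If the multiplicity adjustment were applied to the baseline tests, a Bonferroni version with 20 variables gives 1 − (1 − .05/20)^20 = 4.9%. The rule would then select almost nothing and the models would be left essentially unadjusted.

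**Step 2: how often it selects sex.** With 1050 participants in three arms, an assumed 60% of one sex and 3000 simulated trials, sex reached p < .05 in 0 trials under sex-stratified randomisation in blocks and in 4.8% under simple randomisation.

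**Step 3: what it costs.** Two arms of 350 were simulated with 25% vs 32% abstinent, a logistic model at one time point, two-sided .05 and 3000 runs per scenario. The Monte Carlo error of each power figure is √(.54 × .46 / 3000) ≈ 0.9 points. The analyses were applied to the same simulated trials, so differences between them are less noisy than that. Prognostic strengths are assumed, because the article gives none.

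| Scenario | Unadjusted | Sex only | Sex + covariate | Baseline-test rule |
|---|---|---|---|---|
| Sex OR 1.3, no other predictor | 53.3% | 53.6% | – | – |
| Sex OR 2, no other predictor | 54.0% | 54.9% | – | – |
| Sex OR 1.3, covariate OR 1.5 per SD | 53.7% | 53.8% | 55.1% | 53.9% |
| Sex OR 1.3, covariate OR 2 per SD | 53.3% | 53.5% | 56.7% | 53.6% |

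Sex alone is worth 0 to 1 point and a prognostic covariate about 1 to 3. The baseline-test rule keeps almost none of the gain. With no treatment effect, rejection rates lay between 4.7% and 5.7% for every approach, which is about 5%.

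**Step 4: the shift in the odds ratio.** Unadjusted, 32% vs 25% is (.32/.68)/(.25/.75) = 1.41. Solving for the conditional log odds that reproduce 25% and 32% on averaging over a standard normal covariate gives a conditional odds ratio of 1.43 when that covariate has OR 1.5 per SD, and 1.46 when it has OR 2. The shift is small, but under the rule it is decided by chance imbalance.

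**The case against.** The strongest reply has four parts.

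**The text does not close the list.** It says imbalanced variables will enter, not that only they will. The article is condensed, and a fuller analysis plan may name sex and other covariates. This stands as a limit on wording. A reader might infer that the rule excludes sex by construction. The article does not support that, because it neither bars other covariates nor states that strata are blocked. The rule itself, however, is stated outright and is not a detail left open. An analysis plan that follows it inherits the fault, and one that departs from it contradicts the article.

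**The rule is written in advance and uses baseline data only.** This stands too. A reader might infer that the model is chosen after seeing outcomes. It is not. What is data-dependent is the covariate set, through baseline imbalance.

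**The harm is small.** Type I error stays near 5%, and the gain from sex alone is close to simulation noise. A reader might infer that leaving out sex invalidates the standard errors or the test, but the simulations show no sign of this. The 43% to 64% is the chance that a covariate is added, not the chance of a wrong conclusion.

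**The size of the power loss rests on assumptions.** It does. If covariates explained 10% of outcome variance (itself an assumption), the effective size would be 350/.9 = 389 per arm and power about 58%, up from 54%. That is a shortcut for a continuous outcome. Abstinence is binary, and the simulated logistic analyses give 55% to 57%. Nor does the low power at 350 per arm strengthen this point, since it belongs to the sample-size question.

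None of this supplies a reason to choose covariates by testing for imbalance.

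**Conclusion.** The point holds in a limited form. The article fixes a poor selection rule: it follows chance imbalance, leaves the covariate set unsettled until the baseline tests are run, and gives sex practically no way into the models. Sex would almost never be selected with blocked strata, and about 5% of the time without them.

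The consequence is modest. It consists of a model not fixed in advance, a conditional odds ratio that moves slightly with the covariates selected, and forgone power of about 0 to 1 point for sex and 1 to 3 points for a prognostic covariate. Validity of the test is not in question.

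The selection probabilities assume independent tests at .05. The power figures assume a 60% share of one sex, the stated odds ratios and a single-time-point logistic model in place of the full GLMM. The change is worth making because it settles the primary model before outcomes are analysed and costs almost nothing.

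**What to change.** - Delete the rule that enters variables found to differ at baseline.
- State that the primary and secondary outcome models adjust for sex, as the stratification factor, and for a short named list of baseline variables already collected and expected to predict quitting, whatever their balance. Candidates are time to first cigarette, smoking level and readiness to quit. The article gives no evidence of their prognostic strength in this population, so the investigators should justify the list on subject-matter grounds before outcomes are seen.
- Report baseline characteristics by arm descriptively, without p-values.
- If adjustment for imbalanced variables is still wanted, keep it as a sensitivity analysis only.

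The cost is one paragraph of protocol or analysis-plan wording. No new data, visits or participants are needed.

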### Ethics, safety, and dissemination

This study has been approved by the Case Western Reserve University Institutional Review Board (IRB). This is considered a minimal risk study, which includes state quitline services that are currently available to eligible callers, and adds a video-based intervention to two-thirds of the sample. Thus, all participants have the opportunity to receive standard care (counseling plus NRT) from the quitline. Individuals who are eligible for participation provide verbal informed consent at the time of enrollment, followed by a written information sheet that is mailed to participants. The smoking cessation intervention is delivered by the quitline per their standard operating procedures. The addition of two video-based adjuncts are not anticipated to require early stopping. Quit Coaches have been trained on the goals and procedures of the study, including screening, consenting, and incorporating the video content as appropriate into coaching calls. The principal investigators review a subset of coaching calls and provide performance feedback.

The study provides up to 2 weeks of nicotine patches, which is standard through the quitline. Using data collected from callers, Coaches provide decision support using a database-supported algorithm based on current scientific evidence and the product manufacturer use instructions for dosing. Written materials outlining the appropriate use of cessation support products also accompany the NRT shipment. Participants can contact QuitlineNC at any time if they experience any discomfort from NRT use or have questions. Participants will be directed to cease NRT use and contact their medical provider if they experience distressing or persistent side effects. Adverse events are reported to the IRB annually (for non-serious events) and within three business days (for serious events).

This trial has been approved by the Case Comprehensive Cancer Center Protocol Review and Monitoring Committee (PRMC). There is a data safety and monitoring plan, which includes multiple processes to ensure data safety. Alere Wellbeing is a HIPAA-covered entity and follows all requirements for data safety and confidentiality. In accord with our data use agreement, data transfers from the quitline to the university are completed through a secure server dedicated to the study. Restricted internal use only data are entered and stored on password-protected institutional servers and in locked files. Materials for saliva collection are labeled with participant identification numbers and non-labeled envelopes, and samples are discarded following analysis. Personally identifying information is not collected via the Internet, and para-data are used to estimate online views for the two programs. Weekly audits are conducted to confirm the entry and accuracy of data for new participants. Quarterly audits of the study, using checklists to document accuracy, are conducted independently of the investigators and sponsor. The progress of the trial is reported at 6-month intervals to the PRMC and annually to the IRB. Any personnel or protocol modifications are reported to the IRB.

The *PTF* video is available for non-commercial use through the National African American Tobacco Prevention Network. The data generated from this project is owned by Case Western Reserve University. Data collected as part of quitline registration is owned by QuitlineNC. De-identified datasets will be shared with the scientific community for research following the initial dissemination of the primary study aims, while carefully observing standards of patient privacy, confidentiality, and management of health information. Requests will be made to the PI and will also be subject to approval by QuitlineNC.

## Discussion

This semi-pragmatic RCT is the first to test the effects of a culturally specific video intervention combined with standard quitline counseling among African Americans. Innovations include implementation of the *PTF* intervention in a real-world context, examination of whether cultural specificity increases treatment engagement, consideration of individual differences that may influence treatment response, and examining the feasibility of online intervention delivery. Planned moderator analyses will also yield important insight regarding who is most benefitted by the culturally specific adjunct.

Quitlines represent a core population-based intervention with the potential to reduce barriers to help-seeking and meet the needs of underserved populations. In practice, providing culturally specific care through quitlines is a challenging task. Reasons include the extensive background and training needed, and the numerous racial/ethnic and cultural groups in the US. Moreover, tobacco use is a behavioral problem that may not seem connected to ethno-cultural factors (although it is); thus, the inclusion of a culturally specific intervention component may not be on the list of priorities for state quitlines. However, enhancing quitline services with an evidence-based approach targeting African American smokers might result in a substantial reduction in tobacco cessation disparities. One way to improve the care provided to African American quitline callers, who are disproportionately of low socioeconomic status and medically underserved, is to provide extensive training to Quit Coaches on the unique barriers often faced by this population (e.g., disproportionately high rates of health problems, major life stressors, discrimination) so that culturally specific counseling can be delivered. Another, likely more cost effective approach is to continue to provide standard care, but include the provision of an evidence-based, culturally specific enhancement. The current study offers this approach. If successful, the *PTF* intervention has the potential to be scaled at the national level.

There are several potential weaknesses of this study. The sample includes treatment-seeking tobacco smokers who may differ from non-treatment seekers. This might limit generalizability; however, the limited exclusion criteria reduce this concern. This trial is embedded within a real-world service delivery model; thus no alterations can be made in eligibility for quitline enrollment (vs. study enrollment) or the quitline counseling approach. The sample is also limited to residents in a single state, and may not represent tobacco smokers in other regions of the country. Finally, the ability to evaluate intervention effects is predicated on participants viewing the videos. As such, we are implementing an engagement protocol consisting of bi-weekly and monthly contacts to prompt intervention use and Quit Coaches are trained to refer participants to relevant areas of the videos during coaching calls.

Overall, this study will address important, unanswered questions that have the potential to change best practices for addressing tobacco use among African Americans, particularly those who use the quitline. If our hypotheses are supported, the *PTF* video could be disseminated to all 50 state quitlines, in addition to other delivery channels. The ultimate goal is to eliminate tobacco cessation disparities.

## Abbreviations

DVD: Digital video disc
GLMMs: Generalized linear mixed models
IRB: Institutional Review Board
NAQC: National American Quitline Consortium
NRT: Nicotine replacement therapy
PRMC: Protocol Review and Monitoring Committee
PTF: Pathways to Freedom: Leading the Way to a Smoke-Free Community
QuitlineNC: North Carolina State quitline
RCT: Randomized controlled trial
TLFB: Time-line follow-back
